### Hypothesis

The authors hypothesize that the group submitted to OVM will experience more beneficial effects compared with similar individuals who receive placebo visceral techniques.

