### Sample size calculation

The sample size was calculated using G Power 3.1.9.2 software. This calculation was based on the detection of a 10-point difference on the ODI and 2.5-point difference on the NPRS, which have been identified as the minimum clinically important differences [33]. A sample size of 32 participants per group would provide a 90% power to detect a clinically important difference between groups, assuming a common standard deviation of 12 on the ODI [34] and 3.0 on the NPRS and a two-sided hypothesis with an alpha level of 0.5. The sample will be increased by 20% to compensate for possible dropouts, leading to 38 individuals in each group (overall sample = 76 participants).

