### Statistical analysis

Statistical analysis will be performed using intention-to-treat analysis. If data losses occur during the study, the last observation will be carried forward to adjust the missing data in follow-up evaluations. The Shapiro–Wilk test will be used to determine the normality of the data. Anthropometric differences between groups will be determined using the independent t-test for data will normal distribution and the Mann–Whiney test for data with non-normal distribution. Repeated-measures analysis of variance (ANOVA) followed by the Bonferroni post hoc test will be used to determine the effects of treatment with regard to the NPRS, RMDQ, FFT, FABQ, and EMG considering the following interactions: group (OVM and SOVM) vs evaluation (pre-interventions, after one session, after six weeks, and three months after randomization) vs movement (flexion extension). If the data exhibit non-normal distribution, Friedman’s ANOVA will be used with Dunn’s post hoc test. A *p* value < 0.05 will be considered indicative of statistical significance. The data will be organized and tabulated using the Statistical Package for the Social Sciences (SPSS, v.19.0).

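### For any outcome judged non-normal, the plan switches to Friedman's ANOVA with Dunn's test, which cannot compare OVM with sham

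*Protocol article*

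**What the plan says.** All of the following is in the protocol article.

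- **Hypothesis:** it is a comparison of arms, namely that "the group submitted to OVM will experience more beneficial effects compared with similar individuals who receive placebo visceral techniques".
- **Sample size calculation:** the number per group is set for the "detection of a 10-point difference on the ODI and 2.5-point difference on the NPRS" between groups, "assuming a common standard deviation of 12 on the ODI [34] and 3.0 on the NPRS".
- **Statistical analysis, main route:** "Repeated-measures analysis of variance (ANOVA) followed by the Bonferroni post hoc test will be used to determine the effects of treatment". The factors crossed are "group (OVM and SOVM) vs evaluation (pre-interventions, after one session, after six weeks, and three months after randomization") and movement. This route contains the arm comparison.
- **Statistical analysis, gate:** "The Shapiro–Wilk test will be used to determine the normality of the data".
- **Statistical analysis, fallback:** "If the data exhibit non-normal distribution, Friedman’s ANOVA will be used with Dunn’s post hoc test".
- **Statistical analysis, baseline:** "Anthropometric differences between groups will be determined using the independent t-test" or, if non-normal, a Mann–Whitney test. This is the only place where a between-group rank test is named, and it covers anthropometric variables only.

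**The concern.** The fallback replaces a model that contains group by a test that does not. Friedman's test ranks each patient's own values across visits, and Dunn's procedure after it then compares pairs of visits. Neither uses the arm to which the patient was randomised.

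The test could be run in three ways, and none tests OVM against sham:

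- Pooled over arms, it asks only whether scores change over time.
- Run in each arm, it gives two separate within-arm results.
- Run over group-by-visit columns, it treats unrelated patients as matched.

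At stake is whether the randomised comparison is tested at all for an outcome that takes this route, and that could be a primary outcome. The normality test would then decide not only how the hypothesis is tested but whether it is.

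**Working it through.** **1. The plan's own figure is for a comparison of arms.** The standardised difference is 10/12 = 0.833 for ODI and 2.5/3.0 = 0.833 for NPRS. By the normal approximation, n per group = 2(1.960 + 1.282)²/0.833² = 2 × 10.51/0.694 = 30.3, so 31. The two-sample t-test needs 31.25, so 32, and at 32 its power is 90.7%. The stated 32 per group and 90% power are therefore reproduced for a two-group test at two-sided 0.05. (The sample-size section prints alpha as 0.5, which would give 12 per group; that is a separate matter.) The 20% increase gives 32 × 1.2 = 38.4, stated as 38.

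**2. The fallback contains no arm.** With n patients, k visits and rank sums R_j per visit,

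Q = 12/[n k (k+1)] × Σ R_j² − 3n(k+1).

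The group label does not appear. Reordering the patients in a simulated set of 64 left Q at 2.094 before and after.

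**3. How often the gate would open.** The article gives no expected means, so these are assumptions. Scores were drawn from a normal distribution, rounded, and clipped to the scale (ODI in 2-point steps, SD 12 from the sample-size section). The test level is 0.05.

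| Outcome | Assumed mean / SD | n | Shapiro–Wilk rejects |
|---|---|---|---|
| NPRS | 5 / 2.5 | 38 | about 14% |
| NPRS | 5 / 2 | 38 | about 24% |
| NPRS | 4 / 2.5 | 38 | about 26% |
| NPRS | 5 / 3.0 | 38 | about 27% |
| NPRS | 4 / 3.0 | 38 | about 48% |
| NPRS | 3 / 2.5 | 38 | about 74% |
| NPRS | 2.5 / 2.5 | 38 | about 94% |
| NPRS, arms pooled | 4–5 / 2–2.5, and 5 / 3.0 | 76 | about 58–91% |
| ODI | 25–40 / 12 | 38 | about 4–6% |
| ODI | 20 / 12 | 38 | about 11% |
| ODI | 15 / 12 | 38 | about 44% |

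**4. What the fallback would report.** The set-up is 32 per arm, SD 3.0 from the plan, three visits, within-patient correlation 0.5 (assumed) and 4,000 runs. The last column is Mann–Whitney on change from the first to the second visit.

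| True improvement, OVM / sham | Pooled Friedman significant | One arm only significant | Mann–Whitney on change |
|---|---|---|---|
| 1.25 / 1.25 (no effect) | 83% | 51% | 4.6% |
| 1.5 / 1.5 (no effect) | 94% | 43% | 4.6% |
| 2.5 / 2.5 (no effect) | 100% | 3% | 4.6% |
| 1.25 / −1.25 (2.5-point effect) | 3.8% | 51% | 89% |
| 2.5 / 0 (2.5-point effect) | 77% | 94% | 90% |

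The one-arm-only column can be checked by hand where there is no effect. If each arm is significant with probability p, exactly one is with probability 2p(1−p). At p = 0.51 this is 2 × 0.51 × 0.49 = 0.50, and at p = 0.67 it is 2 × 0.67 × 0.33 = 0.44. It cannot exceed 50%, so the simulated 51% with no effect is simulation error around that ceiling. At 38 per arm, with between- and within-patient SDs of 1.4, within-arm significance of 26% for a common 0.5-point improvement gives 2 × 0.26 × 0.74 = 38%. Significance of 80% for 1.0 point gives 2 × 0.80 × 0.20 = 32%. For a common improvement of 2 points it is about 0.

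**The case against.** The strongest reply is that the main analysis is sound on this point. The repeated-measures ANOVA has group and its interaction with evaluation, and the fallback applies only to outcomes judged non-normal. That stands. A reader might infer that the trial as a whole would lose its OVM-versus-sham comparison; the document does not support this. ODI, away from the floor of its scale, would usually stay on the ANOVA route.

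A reader might also infer that the switch is almost certain for pain. That needs low means, or a rule that one rejected arm-by-visit cell is enough. The article says neither which data are tested (raw scores, changes or residuals) nor what counts as a failure.

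Thirdly, a reader might infer that the trial would report a false benefit because OVM changed significantly and sham did not. The article does not say that Friedman's test will be run in each arm or that arms will be compared by significance status, so this is one possible use and not a planned one.

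One could add that the authors would surely use Mann–Whitney as well, or that the analysis plan will settle it. The text gives Mann–Whitney only to anthropometric variables. The point is also not an omission: the article states a specific fallback, and that fallback cannot answer its hypothesis.

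**Conclusion.** The point holds in conditional form. For each outcome judged non-normal, the plan replaces a between-group analysis with a within-patient one and names no valid test of OVM against sham. This follows from the form of the test and needs no assumption.

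The frequency does rest on assumptions. For NPRS at 38 per arm it runs from about 14–27% for most mid-scale settings, through about half at mean 4 with SD 3.0, to 74–94% at means 2.5–3. Pooling the arms raises the mid-scale figures to 58–91%. For ODI it is near the nominal 5% unless scores lie close to zero. The simulated scores are idealised and take no account of the entry minimum of 2 points on the NPRS.

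The per-arm discordance with no treatment effect, from almost 0 to about 50%, likewise depends on the assumed SD and common improvement. It shows why running the test in each arm would not repair the gap. A between-group rank test keeps about 5% type I error and, at 32 per arm, about 89–90% power for a 2.5-point difference.

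**What to change.** For the outcomes, delete the Friedman/Dunn fallback and state one between-group analysis that is reported whatever the normality test shows. Either of these would do:

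- Keep the planned group-by-evaluation model, baseline-adjusted if wished, with bootstrap or permutation inference where the distribution is in doubt.
- Name Mann–Whitney on change from baseline, at six weeks and at the three-month visit, as the non-normal fallback or as a sensitivity analysis.

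Analyse skewed EMG ratios on the log scale. The planned ANOVA need not be replaced to cure this defect, and the Shapiro–Wilk choice between t-test and Mann–Whitney for anthropometric variables may stay.

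The cost is a change of wording and slightly more analysis work. No extra patients, visits or measurements are needed. The change should be made before outcome data are examined by arm.

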### Adverse events and safety

Adverse events (AEs) are recorded as part of the data collection for each session and will be reported to the clinical authorities and to the ethics committee. Participants suffering AEs will be referred for appropriate treatment.

### Compliance and blinding assessment

To assess patients’ blinding to treatment allocation, patients are asked post treatment (six weeks after the start of treatment) to report which study treatment they think that they received (OVM/SOVM). The effect of their reports on outcome will be examined in explorative analysis.

## Discussion

This paper presents a detailed description of a prospective, placebo-controlled, assessor-blinded, clinical RCT designed to demonstrate the effect of a six-week OVM program on the FRP in individuals with non-specific chronic LBP and functional constipation. It will also allow us to investigate neurophysiologic and biomechanical processes that may contribute to the therapeutic effects of OVM. Analyzing FRP measured in patients with LBP submitted to OVM may help clarify the contributions of passive and active structures during and following OVM, thereby providing evidence for suspected therapeutic mechanisms. The results will be published and the evidence found may contribute to the use of visceral manipulation for this population.

The results and practical relevance of our study will be of importance not only for researchers and policy makers but also for patients suffering from non-specific chronic LBP and functional intestinal constipation.

Given the nature of the study, the limitation of the study is that the therapist will not be blinded. Nevertheless, the design also has important strengths: reproducibility; and the blinding of the assessor and participant. The outcome will provide evidence-based conclusions regarding the effectiveness of this treatment for the management of patients with non-specific chronic LBP and functional constipation.

### Trial status

Participants will be recruited to start in January 2018. Data collection will be finished in May 2018 and study completion is expected to be July 2018.

## Abbreviations

ANOVA: Analysis of variance
CAPES: *Coordenação de Aperfeiçoamento de Pessoa de Nível Superior*
CONSORT: Consolidated Standards of Reporting Trials
EMG: Electromyographic
FAPEMAT: *Fundação de Amparo á Pesquisa do Estado de Mato Grosso*
FFT: Fingertip-to-floor test
FRP: Flexion-relaxation phenomenon
FRR: Flexion-relaxation ratio
LBP: Low back pain
MVC: Maximal voluntary contraction
NPRS: Numeric Pain Rating Scale
ODI: Oswestry Disability Index
OVM: Osteopathic visceral manipulation
RMS: Root mean square
SENIAM: Surface electromyography for non-invasive assessment of muscles
SOVM: Sham osteopathic visceral manipulation
SPSS: Statistical Package for the Social Sciences
